## Abstract

**Background::**

Early treatment initiation is one of the strongest predictors of good treatment response in axial spondyloarthritis (axSpA). Recently, the Assessment in SpondyloArthritis International Society (ASAS) defined early axSpA as a diagnosis of axSpA with a duration of axial symptoms equal to or less than 2 years. Tofacitinib is a Janus kinase (JAK) inhibitor for the treatment of ankylosing spondylitis.

**Objectives::**

Compare the efficacy and safety of tofacitinib versus placebo (both on non-steroidal anti-inflammatory drug (NSAID) background) in patients with active early axSpA and inadequate response to at least one NSAID.

**Design::**

This is a phase IV, randomized, double-blind, placebo-controlled, multicenter clinical trial.

**Methods and analysis::**

The study will recruit 104 patients aged ⩾18 and ⩽45 years with active early axSpA (chronic back pain ⩽2 years), inadequate response to at least one NSAID, and objective signs of active inflammation (on magnetic resonance imaging (MRI) of sacroiliac joints (SIJs) or elevated C-reactive protein). Patients will be randomized 1:1 to receive tofacitinib 5 mg twice daily or placebo, with background naproxen 500 mg twice daily for 16 weeks. Patients not meeting early treatment response criteria at week 4 will receive open-label tofacitinib until week 16. Primary and key secondary endpoints at week 16 will be the proportion of patients achieving disease remission (Axial Spondyloarthritis Disease Activity Score <1.3) and change from baseline in MRI SIJ Spondyloarthritis Research Consortium of Canada osteitis score, respectively. Safety will be monitored up to 4 weeks after the last study drug dose.

**Ethics::**

The study will be performed according to the ethical principles of the Declaration of Helsinki and will be approved by independent ethics committees of each center.

**Discussion::**

This is one of the first randomized clinical trials designed to evaluate the efficacy and safety of a JAK inhibitor in the recently ASAS-defined “early” axSpA population.

***Trial registration*:** ClinicalTrials.gov: NCT06112665; CTIS: 2023-505050-18-00.

## Introduction

Axial spondyloarthritis (axSpA) is a chronic inflammatory rheumatic disease, primarily affecting the spine and sacroiliac joints (SIJ), and is characterized by symptoms such as chronic back pain and stiffness, with eventually arthritis and enthesitis. In addition, patients can present extra-musculoskeletal manifestations such as uveitis, psoriasis, or inflammatory bowel disease. Patients can be classified into two categories: radiographic axSpA (r-axSpA) also named ankylosing spondylitis (AS), with visible structural damage on the SIJ on radiographic imaging; and non-radiographic axSpA (nr-axSpA), without such radiographic structural changes in the SIJ. The global prevalence of axSpA varies among different geographic regions, ranging from 0.3% to 1.4%.^
1
^

In recent years, the concept of “early axSpA” has gained attention, referring to patients in the initial phase of the disease. Definitions of “early” have been based on different aspects, with some researchers focusing on the duration of the disease and others on the absence of irreversible structural damage.^
2
^ The Assessment of SpondyloArthritis International Society (ASAS) aimed to establish a consensus and standardized definition for the term “early axSpA” based on evidence and expert opinion^
2
^ to bring consistency to the study populations in research focused on patients with axSpA at the early stage of the disease. This definition for early axSpA was approved in January 2023 during the Annual ASAS Meeting as follows: “patients with a diagnosis of axSpA with a duration of axial symptoms equal to or less than 2 years. Axial symptoms should include spinal/buttock pain or morning stiffness; regardless of the presence/absence of radiographic damage and should be considered by a rheumatologist as related to axSpA.”^
3
^

The treatment of patients with axSpA has evolved along with the advancements in diagnosis, and the recommendations for their management have been recently updated by the ASAS/European Alliance of Associations for Rheumatology.^
4
^ Non-steroidal anti-inflammatory drugs (NSAIDs) are still considered the first-line therapy, followed by treatment with tumor necrosis factor (TNF) inhibitor, interleukin-17 (IL-17) inhibitor, or Janus kinase (JAK) inhibitor if high disease activity persists despite previous treatment with NSAIDs or when intolerance or contraindications to NSAIDs exist (current practice is to start with a TNF inhibitor or IL-17 inhibitor).^
4
^

Tofacitinib is an oral JAK inhibitor and a targeted synthetic disease-modifying antirheumatic drug (tsDMARD), that has been investigated for the treatment of several immune-mediated diseases^5–10^ and is approved for adult patients with rheumatoid arthritis, psoriatic arthritis, ulcerative colitis, AS, and patients 2 years and over with polyarticular juvenile idiopathic arthritis and juvenile psoriatic arthritis.^11,12^ In the pivotal phase III study in patients with active AS (including those who were bDMARD naïve or had a previous history of TNF inhibitor use), tofacitinib demonstrated superior clinical efficacy, with rapid and sustained response across disease activity measures and quality of life-related outcomes.^
9
^ Further research supported these findings, showing that tofacitinib reduces spinal and SIJ inflammation, as measured by the Spondyloarthritis Research Consortium of Canada (SPARCC) MRI score after 12 weeks of treatment in patients with AS, and is associated with greater clinical responses.^
13
^ Recently, data from phase II/III and phase III multicenter, randomized, double-blind, placebo-controlled clinical trials evaluating Upadacitinib, another drug from the JAK inhibitor family, have demonstrated benefit in patients with active axSpA (radiographic and non-radiographic), supporting further use of this mode of action in this disease area.^14,15^

Growing evidence supports the benefits of early treatment in axSpA, positioning early intervention not only as one of the strongest predictors for good treatment response in axSpA^
16
^ but also as a potential predictor of drug-free remission.^17,18^ Studies such as the ESTHER study (axSpA patients with less than 5 years of symptom duration) and the INFAST study (axSpA patients with less than 3 years of disease duration) suggested a higher probability of remission.^17,18^ In these studies, the remission rate reached approximately 50%, notably higher than the 7%–16% observed in studies with patients with advanced disease stages, as evidenced in pivotal phase III studies with TNF inhibitors,^19–23^ IL-17 inhibitors,^24–26^ and JAK inhibitors.^9,14^ Thus, the proposed study aims to address the following important and so far, unclear aspects of the treatment of axSpA: (i) what is the probability of remission achievement with an advanced therapy in patients with early axSpA (up to 2 years of symptom duration) and (ii) is there a difference in efficacy between an NSAID given alone (as the standard of conventional therapy) and a combination of tsDMARD and NSAID at this early disease stage?

## Methods

### Aim and objectives

The main objective of this study is to evaluate the efficacy of tofacitinib versus placebo (both given on a background of NSAID treatment) in achieving disease remission at week 16 in patients with active early axSpA (back pain ⩽2 years) who have had an inadequate response to at least one NSAID. In addition, the efficacy of tofacitinib versus placebo in reducing MRI inflammation in the SIJ, early treatment response from weeks 1 to 4 (including the effect on patient-reported outcomes (PROs)), and very early (within the first week) response on pain reduction, as well as safety and tolerability of tofacitinib compared to placebo will be evaluated.

### Study population and design

This is a randomized, double-blind, placebo-controlled multicenter study.

The study population will consist of patients aged ⩾18 and ⩽45 years who have a clinical diagnosis of axial SpA and fulfill the ASAS classification criteria for axSpA (classified as either non-radiographic or radiographic according to ASAS criteria) with back pain duration ⩽2 years and inadequate response to at least one NSAID. In addition, for inclusion in the study, patients will be required to show high disease activity defined as Bath Ankylosing Spondylitis Disease Activity Index (BASDAI) ⩾4 and back pain ⩾4 (corresponding to BASDAI Q2, on a numerical rating scale (NRS)) plus either elevated (>5 mg/L) C-reactive protein (CRP) or active inflammation on MRI of the SIJ. Patients are required to be naïve to any biologic or targeted synthetic DMARDs. The list of key inclusion and exclusion criteria is shown in Table 1.

**Table 1. table1-1759720X251324429:** Key inclusion and exclusion criteria for the FASTLANE study.

Inclusion criteria
• Subject ⩾18 and ⩽45 years of age at the screening visit. • Written informed consent. • Clinical diagnosis of axSpA. • Fulfilment of ASAS classification criteria for axSpA. • Symptom (back pain) duration for ⩽2 years, according to the definition of “early axial SpA” by ASAS. • Active disease activity as defined by: (a) BASDAI ⩾4 and back pain score (BASDAI Question 2) of ⩾4 (on a 0–10 NRS) at screening and baseline. and (b) Objective signs of inflammation at screening, evident by: (i) MRI with SIJ inflammation (assessed by two central readers) and/or (ii) Elevated serum CRP levels (>5 mg/L). • History of an inadequate response to at least one NSAID, other than naproxen.
Exclusion criteria
• Current or past treatment with biologic or targeted synthetic DMARD. • Contraindications for MRI or treatment with tofacitinib. • Any active significant acute or chronic infection (at the discretion of the investigator). • History of disseminated/multidermatomal herpes zoster/simplex or history of recurrent herpes zoster. • Patients positive for HIV, hepatitis B, or C at randomization. • Pregnant, breastfeeding, or plan to become pregnant during the study women. • Current malignancy or history of malignancies except adequately treated or excised basal cell or squamous cell carcinoma or cervical carcinoma in situ. • Live vaccinations within 6 weeks prior to baseline.

ASAS, Assessment of SpondyloArthritis International Society; axSpA, axial spondyloarthritis; BASDAI, Bath Ankylosing Spondylitis Disease Activity Index; CRP, C-reactive protein; DMARD, disease-modifying antirheumatic drug; HIV, human immunodeficiency virus; MRI, magnetic resonance imaging; NRS, numerical rating scale; NSAID, non-steroidal anti-inflammatory drug; SIJ, sacroiliac joint.

The study will include a 6-week screening period, a 16-week treatment period, and a safety follow-up at week 20. During the screening period, patients will be assessed for study eligibility and will undergo procedures outlined in the assessment schedule (Table 2). The baseline MRI of the SIJ will be performed within this period to assess the presence of active inflammation (bone marrow edema/osteitis) compatible with axial SpA (as assessed by two independent central readers, and an additional independent reader in case of disagreement) according to ASAS definition for positive MRI (“active sacroiliitis”).^
27
^ At baseline, eligible patients will be randomized on a 1:1 ratio by r-axSpA/nr-axSpA and elevated CRP/non-elevated CRP strata to receive either tofacitinib 5 mg two times daily (BID) plus naproxen 500 mg BID or matching tofacitinib placebo plus naproxen 500 mg BID for a 16-week double-blind treatment period (Figure 1). After the baseline visit, face-to-face clinical assessment will take place at weeks 4 and 16. An evaluation for early treatment response will be performed at week 4. Patients who maintain high disease activity according to BASDAI ⩾4 and demonstrate <20% improvement in BASDAI from baseline at week 4 will receive tofacitinib 5 mg BID open-label until week 16. After the last tofacitinib dose at week 16 or in case of early termination (only in patients who remained on treatment for at least 4 weeks during the study), primary, key secondary, and other efficacy secondary endpoints will be assessed. MRI of the SIJ will be performed in a maximum time window of ±7 days from the last visit.

**Table 2. table2-1759720X251324429:** Study procedures and timelines of the FASTLANE study.

Study procedures	Screening ⩽6 weeks	Baseline week 0	Week 4^ a ^	Week 16^ a ^/ET^ b ^	Week 20^ a ^/FU
	Visit 1	Visit 2	Visit 3	Visit 4	Visit 5 (phone)
Informed consent	X				
Inclusion/exclusion criteria	X	X^ c ^			
Randomization		X			
Demographics	X				
Medical/surgical history including VTE and cardiovascular risk assessment (SCORE2)	X	X^ c ^	X	X	
Contraception check^ d ^	X	X	X	X	X
Vaccination status	X				
Prior/concomitant medication	X	X	X	X	X
Vital signs^ e ^	X	X	X	X	
Weight and height, BMI		X			
Smoking assessment^ f ^	X	X	X	X	
EMMs ASAS report	X	X	X	X	
Physical examination	X	X	X	X	
44 TJC/SJC		X	X	X	
Enthesitis assessment (MASES)		X	X	X	
Dactylitis count		X	X	X	
PGA (on a 0–10 NRS)	X	X	X	X	
ASDAS_CRP_		X	X	X	
BASDAI (on a 0–10 NRS)^ g ^	X	X	X	X	
BASFI (on a 0–10 NRS)		X	X	X	
ASAS HI		X	X	X	
FACIT-F		X	X	X	
PtGA (on a 0–10 NRS)^ g ^	X	X	X	X	
Nocturnal back pain in the last week (on a 0–10 NRS)^ g ^		X	X	X	
Total pain, total back pain, and nocturnal back pain in the last 24 h (on a 0–10 NRS)^ g ^		X	X	X	
BASMI, chest expansion		X	X	X	
Study drug administration		X	X	X	
Hematology, blood chemistry^ h ^	X	X	X	X	
Lipid profile (fasting samples)^ i ^	X	X	X	X	
CRP	X	X	X	X	
HLA-B27 test^ j ^	X				
Urine pregnancy test^ k ^	X	X	X	X	
HIV, Hepatitis B, and Hepatitis C serologies	X				
QuantiFERON^®^-TB or T-SPOT^®^ TB (or similar IGRA test)^ l ^	X				
Chest X-ray^ l ^	X				
Pelvis X-ray^ m ^	X				
MRI of SIJs	X			X	
ECG	X				
Adverse events		X	X	X	X

a Weeks after the first intake of the study drug, visits have a time window of ±7 days.

b ET = early termination visit for subjects who prematurely discontinue the study for any reason.

c Interim history to check for investigator’s assessment of benefit:risk.

d For pre-menopausal female subjects and non-sterile males only.

e Body temperature, heart rate, blood pressure.

f Former and actual smoking state at screening, pack-years calculation for the former and actual smoker.

g Home-based collection of PROs at Weeks 1, 2, 3, 8, and 12. Total pain, total back pain, and nocturnal back pain in the last 24 h will also be collected daily on days 1–6. PROs at Week 0 will be collected during Visit 2, at Week 4 during Visit 3, and at Week 16 during Visit 4.

h Complete blood count, total bilirubin, ALT, AST, GGT, AP, creatinine, and CK.

i Total cholesterol, LDL cholesterol, HDL cholesterol, and triglycerides.

j To be performed only if there is no HLA-B27 test previously performed (previous results need to be demonstrated by a laboratory or medical report).

k Female patients of child-bearing potential only. High sensitivity urine pregnancy test. A serum pregnancy test is to be performed in case of doubts. A pregnancy test will be performed in all site study visits.

l QuantiFERON^®^-TB, T-Spot^®^ TB test, or similar IGRA test and Chest X-ray performed within 3 months prior to screening will be accepted. In female patients of child-bearing potential, evidence of a negative pregnancy test prior to chest X-ray is required.

m Pelvis X-rays; to be performed at screening only if there is no image performed within 6 months prior to screening and/or previous available imaging does not meet the pre-specified quality requirements. In female patients of child-bearing potential, evidence of a negative pregnancy test prior to pelvis X-ray is required.

ALT, alanine aminotransferase; AP, alkaline phosphatase; ASAS, Assessment of Spondyloarthritis International Society; ASAS HI, ASAS health index; ASDAS, Axial Spondyloarthritis Disease Activity Score using C-reactive protein; AST, aspartate aminotransferase; BASDAI, Bath Ankylosing Spondylitis Disease Activity Index; BASFI, Bath Ankylosing Spondylitis Functional Index; BASMI, Bath Ankylosing Spondylitis Metrology Index; BMI, body mass index; CK, creatinine kinase; CRP, C-reactive protein; ECG, electrocardiogram; EMM, extra-musculoskeletal manifestation; ET, early termination; FACIT-F, Functional Assessment of Chronic Illness Therapy-Fatigue; FU, follow up; GGT, gamma-glutamyl transferase; HIV, human immunodeficiency virus; HLA-B27, human leukocyte antigen B27; MASES, Maastricht Ankylosing Spondylitis Entheses Score; MRI, magnetic resonance imaging; NRS, numerical rating scale; PGA, Physician Global Assessment; PROs, patient-reported outcomes; PtGA, Patient Global Assessment; SCORE2, Systemic Coronary Risk Estimation 2; SJC, swollen joint count; TB, tuberculosis; TJC, tender joint count; VTE, venous thromboembolism.

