**Figure 1. fig1-1759720X251324429:**
[figure not shown]
Study Design of FASTLANE study.

Digitally collected PROs will include total pain, total back pain, and nocturnal back pain in the last 24 h on days 1–6. From week 1, digitally collected PROs will be collected weekly from weeks 1 to 3, and then at weeks 8 and 12; and will also include BASDAI, nocturnal back pain, and patient global assessment (PtGA) during the last 7 days. PROs at screening (BASDAI, PtGA only), baseline, week 4, and week 16 will be collected during the correspondent face-to-face visit.

Safety will be monitored throughout the whole duration of the study up to 4 weeks after the last study drug dose. A comprehensive cardiovascular (CV) and venous thromboembolism (VTE) risk assessment will be performed at each applicable face-to-face visit to maintain an adequate benefit:risk balance for all study participants. For VTE, subjects will be screened for factors such as heart failure, recent myocardial infarction, inherited coagulation disorders, prior VTE, hormone therapy use, malignancies, major surgery, or immobilization. Additional risk factors including age, obesity, diabetes, hypertension, smoking, and family history of VTE will also be considered. Any newly developed risks will prompt reevaluation and possible treatment discontinuation. Similarly, the CV risk assessment will include evaluation using the Systemic Coronary Risk Estimation 2 calculator, along with other factors like atherosclerotic CV disease, uncontrolled diabetes, smoking history, and family history of premature CV events. Continuous monitoring at each visit will ensure timely management of newly emerging risks, promoting patient safety.

This protocol has been developed using the SPIRIT (Standard Protocol Items: Recommendations for Interventional Trials) 2013 statement, a guideline on standard protocol items for clinical trials.^
28
^ SPIRT Checklist for FASTLANE study is available as Supplementary Material.

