At weeks 4 and 16, the proportion of patients achieved: • an ASDAS clinically important improvement • an ASDAS major improvement • ASDAS <2.1 • ASAS20, ASAS40, ASAS partial remission, BASDAI50 responses At weeks 4 and 16 vs baseline, improvement in disease activity, function, axial mobility, and QoL was measured according to: • ASDAS • BASDAI • PGA • CRP • BASFI • BASMI and chest expansion • 44 TJC/SJC for peripheral involvement • MASES for enthesitis • Dactylitis count • ASAS-HI and FACIT-F The proportion of subjects requiring treatment escalation to open-label tofacitinib at week 4 (proportion of subjects with BASDAI ⩾4 plus BASDAI reduction <20% from baseline at week 4) At weeks 1, 2, 3, 4, 8, 12, and 16 vs baseline, improvement in: • total back pain (NRS) (question 2 of BASDAI) in the last 24 h and 7 days • nocturnal back pain (NRS) in the last 24 h and 7 days • total pain (NRS) in the last 24 h • PtGA At day 1–6 vs baseline, improvement in: • Total back pain (NSR), nocturnal back pain (NSR), and total pain (NSR) in the last 24 h At week 16 vs baseline, improvement in EMMs (overall and by EMM type) At week 20 (or 4 weeks after ET), safety and tolerability of tofacitinib vs placebo by incidence of AEs, TEAEs, AEs of special interest,^ a ^ AEs leading to study discontinuation.
*Tertiary/exploratory endpoints*
At week 16, the proportion of patients achieving ASDAS <1.3 by: • radiographic status (nr-axSpA/r-axSpA) subgroup • CRP (elevated/non-elevated) subgroup • sex subgroup (female/male) • tofacitinib early treatment response subgroup (responders at week 4/non-responders at week 4) At week 16 vs baseline, improvement in MRI SIJ SPARCC structural score.^ b ^ At week 16 vs baseline, improvement in MRI SIJ SPARCC osteitis score by: • radiographic status (nr-axSpA/r-axSpA) subgroup • CRP (elevated/non-elevated) subgroup • sex subgroup (female/male) • tofacitinib early treatment response subgroup (responders at week 4/non-responders at week 4).

a AEs of special interest are: all malignancies excluding NMSC, NMSC, MACE, DVT, PE, ATE, GI perforation, hepatic events, DILI, HZ, OI, OI excluding HZ, SIE, and ILD.

b Components include backfill, fat metaplasia, sclerosis, erosion, and ankylosis.

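### The week-20 safety call is timed from first intake, so a call made within its window can fall short of the stated four weeks after the last dose (minor)

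*Protocol article*

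**What the plan says.** The length of post-treatment safety monitoring is stated in two places, both counted from the last dose:

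- Protocol article, Abstract, Methods and analysis: "Safety will be monitored up to 4 weeks after the last study drug dose".
- Protocol article, Study population and design (text after Figure 1): "Safety will be monitored throughout the whole duration of the study up to 4 weeks after the last study drug dose".

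The schedule is built differently. The design section describes "a 16-week treatment period, and a safety follow-up at week 20". In Table 2 the columns for weeks 4, 16 and 20 all carry footnote a: "Weeks after the first intake of the study drug, visits have a time window of ±7 days". Visit 5 at week 20 is a phone contact and the last column in which adverse events are marked.

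The last dose is tied to week 16. The design section introduces the endpoint assessments with "After the last tofacitinib dose at week 16 or in case of early termination", and the Table 2 row "Study drug administration" is marked at baseline, week 4 and week 16.

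Table 3 times the safety endpoint as follows: "At week 20 (or 4 weeks after ET), safety and tolerability of tofacitinib vs placebo". Early terminators are therefore timed from their own termination visit, and completers from first intake.

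**The concern.** The stated property is an interval that starts at the last dose. The schedule fixes both ends of that interval separately from the first dose, each with its own tolerance, and sets no minimum distance between them. The two tolerances can add up, so a site that keeps both visits in window may still make the final safety contact before four weeks have passed.

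What is at stake is the evenness and completeness of adverse-event collection after treatment. Table 3 makes the incidence of adverse events, including events of special interest such as serious infections, herpes zoster and venous thromboembolism, a secondary endpoint assessed at this contact. Under Statistical analysis, the unblinded analysis follows once the last patient has completed week 20 (or the last visit after early termination) and the database is locked. No later scheduled contact would pick up events from the missing days. With 104 / 2 = 52 patients per arm, one event is 1/52, or about 1.9 percentage points, so a single unrecorded event would be visible in a descriptive table.

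**Working it through.** **Inputs (Table 2, footnote a, and the design section)**

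- Week 16 = 16 × 7 = day 112; with ±7 days, day 105 to day 119.
- Week 20 = 20 × 7 = day 140; with ±7 days, day 133 to day 147.
- Stated follow-up: 4 × 7 = 28 days after the last dose.

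**The plan's own figure.** On nominal dates, 140 − 112 = 28 days. The stated four weeks are reproduced.

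**Range allowed by the windows.** Gap = day of call − day of last dose. The article does not say whether a patient with a late week-16 visit goes on dosing until that visit, so both readings are shown.

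| Reading | Shortest gap | Nominal | Longest gap |
|---|---|---|---|
| Dosing continues to the actual week-16 visit | 133 − 119 = 14 | 28 | 147 − 105 = 42 |
| Dosing stops on day 112 whatever the visit date | 133 − 112 = 21 | 28 | 147 − 112 = 35 |

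On the first reading, a patient seen on day 119 reaches 28 days only if the call is made on the last permitted day (119 + 28 = 147).

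**How often, for illustration only.** The document gives no distribution of visit dates. Assume whole-day offsets from −7 to +7, uniform and independent for the two visits: 15 × 15 = 225 pairs.

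- First reading: a gap below 28 days in 105/225 = 46.7%, exactly 28 in 15/225 = 6.7%, above 28 in 105/225 = 46.7%. Below 21 days in 28/225 = 12.4%. Exactly 14 days in 1/225 = 0.4%.
- Second reading: only the call date varies. Below 28 days in 7/15 = 46.7%, above 28 in 7/15 = 46.7%, and never below 21.

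Under this assumption the mean gap is 28 days on both readings.

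**The case against.** The strongest reply is that no two stated values conflict. Week 20 less week 16 is 28 days, and any symmetric window around a nominal 28 days puts some patients below it and as many above. This is right about the nominal dates and the average. It does not remove the shortfall, because the two directions are not equivalent: a late call can still ask about the first 28 days, whereas an early call cannot cover days that have not yet passed.

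The wording could also be taken as an outer limit (up to four weeks) rather than a required length. Short follow-up would then be permitted, but the windows let the call run to 35 or 42 days, beyond the limit. Footnote and statement disagree on that reading too.

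The article is a condensed text, and the full protocol may define an adverse-event collection period that does not depend on the call date. If so, this is a matter of wording in the article. Still, the point does not rest on missing detail: the article itself gives the anchor, the window and the length, and these do not fit together.

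Other parts of the reply stand. A reader might infer that half the follow-up is commonly lost. The documents do not support that: 14 days needs both visits at opposite ends of their windows and also needs dosing to continue to a late visit, which the schedule suggests but does not state. A reader might infer that such a call would count as fully compliant, yet the four-week statements also bind the sites. Nor are early terminators timed strictly from the last dose: their anchor is the termination visit, and nominally both groups are followed for four weeks.

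**Conclusion.** The point holds as a minor inconsistency. Safety follow-up is stated from the last dose but scheduled from the first, and a call within its window can come up to 7 days short of four weeks if dosing stops on day 112 (28 − 21), or up to 14 days short if dosing continues to the actual week-16 visit (28 − 14). That some shortfall is possible does not depend on which dosing reading applies; only its largest size does. The illustrative percentages rest on uniform, independent visit offsets, which the document does not supply, and should not be read as forecasts.

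A reader might go further and infer that the safety comparison is biased. The documents do not support this. Both arms follow the same schedule under blinding, so the unevenness should be similar in each, and the windows lengthen follow-up as well as shorten it. The Statistical analysis section plans descriptive safety summaries and does not say that they assume equal observation time. The primary and key secondary analyses at week 16 are not affected.

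**What to change.** Reconcile Table 2, footnote a, with the four-week statements in the Abstract and the design section. Remove Visit 5 from the first-intake anchor and time it from each patient's last study-drug dose, for completers and early terminators alike, with a window that the sponsor chooses to be consistent with its own stated four weeks. Bring the timing of the safety endpoint in Table 3 into line with the same anchor.

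The cost is one footnote and one table entry. Visit 5 is a phone call, so no site visit is added. The downside is that some calls fall about a week later than now: for a last dose on day 119, four weeks end on day 147, which is 7 days after the nominal day 140 and already the last day of the present window. Any later tolerance would go beyond that day.
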